###### Addressing Biological Variables

As this project is focused on SMMT individuals, rather than assessing the effects of biological sex, we will screen for the effects of gender identity and sexual orientation in the aforementioned modeling framework. This is accomplished by introducing indicator variables for these subgroups into the analyses and assessing statistical and practical significance. The stratified randomization procedure should prevent systematic differences at baseline among the groups. We will check for statistically significant differences after randomization and adjust for such differences in the analysis in the rare event that they manifest.

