#### Description of Study Arms

##### Overview

Participants will be enrolled in the study for 9 months, including the 2-month intervention period and multiple follow-up monitoring periods to assess long-term effects. All participants will begin with a 30-day monitoring period, which will establish baseline alcohol use through daily breathalyzer reading requests and surveys. After this 30-day period, they will complete additional baseline measures (T1) and then begin their assigned intervention, if applicable. After the interventions are delivered, participants will complete an additional self-report (T2). Subsequently, there will be 2 additional monitoring periods and assessments spread across the 9-month study period to assess long-term intervention effects, with some months involving no study activities. A depiction of the participation timeline is included in Figure 2, and details of study activities completed across the study timeline and RCT arms are provided in Table 1.

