###### Baseline and Follow-Up Measures

An assessment battery will be administered to all participants at T1, T2, T3, and T4. This will include several measures of alcohol use as well as more exploratory variables, including alcohol cravings, alcohol consequences, the use of alcohol treatment services, HIV risk behaviors, and experiences of discrimination related to participants’ identity as sexual and gender minority individuals. Table 2 presents a description of the key study measures.

**Table 2 table2:** Description of key study measures.

Construct and time		Measure	End point	Description
Drinking days, 2× daily		Breath alcohol content	Primary	BACtrack Mobile breathalyzer result sent via mobile app; measured 2× daily for 8 weeks during the intervention and for 1 month before T1^a^, T3^b^, and T4^c^; 2 negative readings per day=nondrinking day
Drinks per drinking day, daily		Self-reported alcohol use through app	Secondary	3 items: alcohol consumed (yes or no), number of drinks, and time spent drinking; measured daily during the intervention and for 1 month before T1, T3, and T4
Binge drinking episodes, daily		Self-reported alcohol use through app	Secondary	Occasions when participants had ≥5 drinks based on self-reported number of drinks; measured daily during the intervention and for 1 month before T1, T3, and T4
Alcohol withdrawal symptoms, daily		Single-item AWSC^d^ [40]	Exploratory	1 item: alcohol withdrawal symptom severity on a scale of 0 to 9; those scoring ≥2 are asked to complete the 17-item AWSC, which assesses the severity of symptoms; measured daily during intervention and for 1 month before T1, T3, and T4
Sexual activity, daily		Self-reported through app	Exploratory	6 items: past-day sexual activity, number of partners, partner type, partner HIV status, type of sexual activity, condomless sex, and PrEP^e^ use
Location characteristics, up to 2× daily		Self-reported through app	Exploratory	12 items assessing alcohol and substance use, sexual behaviors, peer use of alcohol or substances, and harassment or discrimination experienced
Alcohol use, T1, T2^f^, T3, and T4		PROMIS^g^ Short Form–Alcohol Use 7a [41]	Exploratory	7 items that assess general alcohol use and problem drinking in the past 30 days (eg, drank too much and drank heavily)

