**Alcohol expectancies**				
	T1, T2, T3, and T4	PROMIS Short Form–Alcohol Use–Negative Expectancies 7a [41]	Exploratory	7 items that assess the negative expectancies of alcohol use (eg, making bad decisions and behaving rudely)
	T1, T2, T3, and T4	PROMIS Short Form–Alcohol Use–Positive Expectancies 7a [41]	Exploratory	7 items that assess the positive expectancies of alcohol use (eg, improves mood and sociability)
Readiness to change drinking, T1, T2, T3, and T4		Readiness to Change Questionnaire [42]	Exploratory	12 items that assess the stage of change toward reducing alcohol use (precontemplation, contemplation, and action)
Drinking refusal self-efficacy, T1, T2, T3, and T4		Drinking Refusal Self-Efficacy Questionnaire–Revised [43]	Exploratory	19 items that assess individuals’ belief in their ability to resist alcohol, with 3 subscales: social pressure drinking, emotional relief drinking, and opportunistic drinking
Sexual risk behaviors, T1, T2, T3, and T4		National HIV Behavioral Surveillance System [44]	Exploratory	≥6 items: number of partners in previous 12 (T1) or 3 (T2-T4) months; partner type (main vs casual); partner HIV status; frequency of condomless sex (anal, vaginal, or oral), transactional sex, and concurrent sex and drug or alcohol use; and PrEP use
Condom attitudes, T1, T2, T3, and T4		Multidimensional Condom Attitudes Scale [45]	Exploratory	16 items that measure attitudes toward condoms across 7 factors: reliability, effectiveness, pleasure, identity stigma, embarrassment about purchase, negotiation, and action maintenance
Perceived HIV risk, T1, T2, T3, and T4		Perceived Risk of HIV Scale [46]	Exploratory	8 items that assess likelihood estimates, intuitive judgments, and salience of HIV risk based on previous behaviors
Discrimination due to sexual or gender identity, T1, T2, T3, and T4		Heterosexist Harassment, Rejection, and Discrimination Scale [47]	Exploratory	12 items that assess harassment, rejection, and family discrimination related to LGBTQ^h^ identities
Alcohol cravings, T1, T2, T3, and T4		Penn Alcohol Craving Scale [48]	Exploratory	5 items that assess alcohol-related cravings; higher scores indicate higher rates of alcohol cravings
Alcohol Use, T1, T2, T3, and T4		Alcohol Quantity Measures	Exploratory	7 items that assess alcohol use over the past 30 days

^a^T1: baseline assessment.

^b^T3: 6-month assessment.

^c^T4: 9-month assessment.

^d^AWSC: alcohol withdrawal symptom checklist.

^e^PrEP: pre-exposure prophylaxis.

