##### Data Analysis Plan

###### Analysis of Alcohol Use Outcomes

Descriptive statistics for breathalyzer reading data will be summarized overall, by group (SAM only, SAM+TRAC, and SAM+TRAC-ER) and across time periods (T1-T4). The primary outcome is the number of drinking days in the past month, which is defined as the days on which individuals did not report 2 negative breathalyzer results. The rate of drinking (incidence of drinking) is the number of drinking days observed within the past month. The secondary outcomes include the number of drinks per drinking day, the number of days with binge drinking episodes, and the number of days for which HIV risk behaviors occur. All these outcomes are count data. The goal of this analysis is 2-fold: first, short-term analysis at the end of the 2-month intervention period, and, second, long-term analysis at the end of 9 months. We will fit a generalized linear model [50], with a general formulation for count data as follows:

g(E(y_i_)) = g(μ_i_) = x'_i_β (1)

where *y_i_* is the outcome variable for (*i*=1,2,3,...,*n*), *n* is the total number of observations, *μ*_i_=*E*(*y_i_*) is the expected count, *g* is the link function (a mathematical function connecting the counts with the explanatory variables), *β* is a vector of regression parameters to be estimated, and *x_i_* is a vector of independent covariates to be included in the model. These covariates include group, time, age (or age group), gender identity, sexual orientation, and site.

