###### Short-Term Outcome Analyses

After 3 months, we will fit the aforementioned model to the data and compare the groups at T1 and T2 while adjusting for the covariates. The PROC GENMOD procedure in SAS (SAS Institute Inc) will be implemented to estimate the parameters of the model, where we specify a log-link function, Poisson distribution for the count data, an offset (which is a function of the total exposure), and the covariates. We will address overdispersion using negative binomial distribution. Overdispersion occurs when the expected count for the outcome variable is not the same as its variance. The generalized estimating equation procedure will be used to account for correlation induced by the repeated observations at T2.

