###### Long-Term Outcome Analyses

At 9 months, the time variable will include observations at T1 to T4, and the procedure implemented for the short-term analysis will be repeated with the inclusion of additional covariates in the form of interaction terms among the groups and follow-up times (T1-T4). The interaction effect is central to the comparison of the groups over the study period. Generalized estimating equation fit criteria and quasi-likelihood under the independence model criterion value will be used to determine the adequacy of model fit. This modeling framework facilitates the easy computation of hypothesis tests and CIs for effects, which will form the basis of our inferential strategy in this project. Specifically, contrast statements will be used to test specific subgroup comparisons. Multiple imputation procedure will be implemented whenever necessary for missing data points. SAS (version 9.4 or higher) will be used for all analyses, and a standard 5% significance level will be used for all statistical tests.

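### On top of its fixed covariates, the plan adjusts for any baseline difference that proves statistically significant, so the final model depends on chance test results

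*Protocol article*

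**What the plan says.** Three parts of the Data Analysis Plan bear on this.

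- Analysis of Alcohol Use Outcomes lists the model terms: "These covariates include group, time, age (or age group), gender identity, sexual orientation, and site". These enter regardless of any test.
- Short-Term Outcome Analyses will "compare the groups at T1 and T2 while adjusting for the covariates", and Long-Term Outcome Analyses extends the same model to T1 to T4 with group-by-time interactions. Baseline drinking is thus already in the model as a repeated observation.
- Addressing Biological Variables first relies on the design: "The stratified randomization procedure should prevent systematic differences at baseline among the groups". It then adds: "We will check for statistically significant differences after randomization and adjust for such differences in the analysis in the rare event that they manifest".

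The article does not say which variables are checked, or whether the check is one three-arm test or three pairwise tests. The level is given in Long-Term Outcome Analyses: "a standard 5% significance level will be used for all statistical tests". No correction for the number of baseline tests is stated.

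**The concern.** With proper randomization the null hypothesis of a baseline test is true by construction, so a small p-value says only that chance produced an imbalance. It does not say whether the variable predicts drinking. A weak predictor with p=0.04 would enter the model, while a strong predictor with p=0.10 would not.

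What is at stake is the specification of the primary model. Its covariates beyond the fixed list would be known only after the baseline data had been tested, and they would not have been chosen for prognostic value. Because the text does not say which variables are tested or how, the analyst also keeps discretion over when the rule fires.

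**Working it through.** **The plan's own figure.** There is none for this rule: the article calls the event rare and gives no number. The sample size figures (324/0.80 = 405) are not affected.

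**Which variables the rule can affect.** Age, gender identity, sexual orientation and site are in the model anyway, so a significant difference on any of them changes nothing. T1 drinking days are already a modelled observation. The rule can alter the model only through other baseline measures.

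**How many there are (own count from Table 2).**
- Questionnaire battery: "An assessment battery will be administered to all participants at T1, T2, T3, and T4". The rows measured at T1 are PROMIS alcohol use, two consequences scales, two expectancies scales, readiness to change, refusal self-efficacy, sexual risk behaviors, condom attitudes, perceived HIV risk, discrimination, cravings and alcohol quantity: 13 rows.
- App and breathalyzer measures: "All participants will begin with a 30-day monitoring period, which will establish baseline alcohol use through daily breathalyzer reading requests and surveys". The rows are drinking days, drinks per drinking day, binge episodes, withdrawal symptoms, sexual activity and location characteristics: 6 rows, for a total of 19.
- Counting subscales raises this. Condom attitudes is described as "16 items that measure attitudes toward condoms across 7 factors" (6 more scores than one row) and refusal self-efficacy has 3 subscales (2 more): 19 + 6 + 2 = 27.

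**Formula.** For k independent tests at 5%, P(at least one significant) = 1 − 0.95^k.
- k = 2 (gender identity and sexual orientation only): 9.8%
- k = 4 (the four fixed covariates): 18.5%
- k = 13: 48.7%
- k = 14: 51.2%, the first value above one half
- k = 18 (all rows except drinking days, already modelled): 60.3%
- k = 19: 62.3%

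For k = 2 and k = 4, stratification would lower the figure for any variable used as a stratification factor.

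**Allowing for correlation.** Several rows measure related aspects of drinking, so independence is an upper bound here. Simulation with equally correlated rows and one global three-arm test per row (20,000 replicates) gave:

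| Rows tested | r = 0 | r = 0.2 | r = 0.3 | r = 0.5 |
|---|---|---|---|---|
| 13 | 48.7% | 45.2% | 41.8% | 34.2% |
| 19 | 62.4% | 57.6% | 52.7% | 41.1% |
| 25 | 72.4% | 66.9% | 61.9% | 47.5% |
| 30 | 78.6% | 72.8% | 66.6% | 51.3% |

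If all three pairwise arm comparisons were tested instead, the range over the same correlations would be 62–82% for 13 rows and 73–92% for 19.

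**Effect on type I error.** The rule was simulated under the null with three arms of 135, a normal outcome, the baseline outcome (correlation about 0.69) always adjusted, and 13 or 19 prognostic covariates added only when p<0.05, at correlation 0 or 0.3 (6,000 runs each). Type I error was 4.1–4.7% with the rule and 4.5–5.0% without it. A repeat with separately chosen covariate strengths also showed no inflation. This is a linear approximation to the planned count model.

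**The case against.** The strongest defence is that the conditional step is a small supplement to a sound model. Four baseline covariates are fixed, and the natural strongest predictor, baseline drinking, is already modelled (within-participant correlation 0.69 in Sample Size Justification). A reader might infer from the sentence that the plan adjusts only for variables that differ significantly. It does not, and little precision is lost on the main predictors.

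A reader might also infer that the trigger is more likely than not to fire. The documents do not support that as a general statement. Nothing says the whole Table 2 battery is tested, and the sentence stands under a heading concerned with gender identity and sexual orientation, where the figure is about 10%. Even the 13 T1 rows reach at most 49% with global tests. Passing one half needs further rows with modest correlation, subscales counted separately, or pairwise testing.

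Nor do the documents support a claim of inflated error. The trigger uses baseline data only, so it cannot select covariates by the treatment effect observed, and the simulation points to slight conservatism at most.

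All of this stands, and it limits the size of the point. It does not rescue the rule. On the narrow reading the rule is redundant, because gender identity and sexual orientation are in the model regardless. Wherever the rule has any effect, it acts on measures outside the list, on a criterion unrelated to prognosis.

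**Conclusion.** The point holds as a flaw in how the model is specified. The harm is a primary model that depends on the data and extra covariates not chosen for prognostic value. It is not a bias in the treatment comparison or a shown loss of error control.

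If the Table 2 battery is checked with one global 5% test per row, at least one chance difference has a probability of about 34–49% (13 rows) or 41–62% (19 rows), so calling the event rare is not supported on that reading. If only gender identity and sexual orientation are checked, it is about 10%, and nothing in the model changes. These figures assume one test per row, equal correlation between 0 and 0.5, and no multiplicity correction. The practical effect on inference is likely to be modest; the change is worth making because it costs almost nothing.

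**What to change.** Delete the sentence on checking for significant differences. In its place:

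- State that the covariates listed under Analysis of Alcohol Use Outcomes (with one form of age chosen), plus the stratification factors, are the final set, fixed before outcome data are analysed.
- Keep T1 drinking days as the repeated baseline observation. Do not also enter them as a covariate, since T1 would then stand on both sides of the model.
- Report baseline balance descriptively by arm, without p-values.
- Label any further adjustment for an observed imbalance a sensitivity analysis.

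The cost is one sentence removed and a few added. Sample size, data collection and conduct are unaffected. The Discussion states that recruitment had not begun as of February 2024, so at the article's date the change could precede all outcome data.

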###### Qualitative Data Analysis

Audio files of postintervention interviews will be transcribed and imported into NVivo software (Lumivero). Each transcript will be examined and coded using a grounded thematic approach [51], drawing on observed themes regarding intervention attitudes, experiences, and effects. The research team will develop the coding scheme based on an initial review of the transcripts; next, 2 coders will independently code a random sample of 10% of the transcripts. Interrater reliability will be assessed, and the coding scheme will be refined if reliability is not acceptable (acceptable interrater agreement: >90%). Once interrater agreement is achieved, the coders will code the remaining transcripts and collect representative quotations.

###### Gender-Inclusive and Gender-Specific Approach to Analysis

As an analytic framing to examine inequities in alcohol behaviors within SMMT populations, we will use gender-inclusive and gender-specific approaches throughout the study’s quantitative and qualitative analyses, following guidelines from Restar et al [52]. Given that there is epidemiological evidence that transgender and cisgender populations’ health outcomes and behaviors, such as alcohol use, are dissimilar to each other and that the drivers of these inequities are contextually uniquely different [6,53-55], applying this approach to our analysis is appropriate. This approach allows our analytical modeling to examine and discern any potential shared versus differential intervention experiences and outcomes across gender groups (ie, between cisgender and transgender participants and within gender subgroups of transgender participants). On the basis of the findings, it will also allow us to provide future intervention recommendations for either the entire sample (ie, gender inclusive) or specific to each gender group (ie, gender specific).

###### Scientific Rigor

The proposed study uses a rigorous randomized comparative effectiveness trial design to assess intervention effects on alcohol use outcomes. The following characteristics add to the rigor of the study: (1) the use of a SAM-only control group so that all groups can be compared using daily-level alcohol use data, (2) the incorporation of breathalyzers to enhance the validity of self-reported alcohol use, (3) the inclusion of follow-up self-report and SAM data to assess long-term outcomes, (4) recruitment strategies that use in-person and web-based methods to enhance the diversity of the sample, (5) the inclusion of a dedicated biostatistician to provide rigorous outcome analyses, (6) support from app programmers to customize the app and address technical issues, and (7) the inclusion of a licensed social worker to ensure high-quality MI training and fidelity.

## Results

The study is part of a 5-year National Institutes of Health research project that was funded in August 2022 by the National Institute on Alcohol Abuse and Alcoholism. The first 1.5 years of the study will be dedicated to planning and development activities, including formative research, app design and testing, and message design and testing. The subsequent 3.5 years will see the study complete participant recruitment, data collection, analyses, report writing, and dissemination. We expect to complete all study data collection in or before January 2027.

As of February 2024, we have published 1 manuscript, a systematic review exploring interventions for addressing alcohol use and sexual HIV risk–related behaviors [16]. We have also completed 2 rounds of focus groups to refine the intervention content and harm reduction messages delivered in TRAC-ER. Overall, 34 participants were enrolled in the first round of focus groups; however, 5 were excluded after further review showed they did not meet the eligibility criteria. This resulted in a final sample of 29 individuals for the first round of focus groups. We enrolled 22 participants for the second round of focus groups. First, we conducted separate focus groups with participants of different gender identities (sexual minority cisgender men, nonbinary and gender nonconforming participants, transgender men, and transgender women) to obtain feedback on harm reduction content added to the intervention manual and to help us generate initial harm reduction messaging. Next, we conducted an additional blended focus group to help us further refine the messages and develop our final *library* of messages that will be programmed into the app. A manuscript describing this process and the results is forthcoming.

## Discussion

### Summary

This manuscript describes the protocol for a 3-arm RCT evaluating the efficacy of a mobile-based EMI for reducing alcohol use and HIV risk behaviors among emerging adult SMMT individuals (N=405). We will compare a monitoring-only control to TRAC, a mobile-based MI intervention, and to TRAC-ER, an intervention combining TRAC with in-the-moment messaging to prevent hazardous alcohol use and reduce harm when participants visit risky locations. Mobile breathalyzers and surveys will be used to collect frequent data on alcohol and HIV risk behaviors. We will assess outcomes immediately before and after the intervention, as well as at 6-month and 9-month follow-ups. The primary outcome is the number of drinking days. Formative development work for this RCT has been completed, with the trial to begin recruiting soon (as of February 2024).

This study will make significant contributions to the literature on alcohol use interventions for SMMT populations. It uses an innovative precision health approach that draws upon the frequent use of smartphone technologies by emerging adult populations and the high acceptability of mobile breathalyzers. Despite the proliferation of mobile devices in society, the field of EMIs remains understudied, with very few RCTs being conducted related to alcohol use. In addition, EMIs have shown initial promise in being paired with MI approaches [56-58]; therefore, the proposed study would help to add to the fledgling evidence base regarding the effectiveness of this approach. The use of mobile technology and remote delivery of the tested interventions means that once the ideal approach is identified in terms of efficacy, the intervention will be easily scalable to individuals across wide geographic areas.

Our study has promising strengths, but it must be considered in light of several limitations. While the use of ecological momentary assessment (EMA) provides advantageous opportunities for real-time trigger location data and convenience reporting through smartphones, prior EMA studies highlight the potential exhaustion that participants may experience, which may reduce the level of participation. This study may further explore convenient assessment windows to diminish the intensity of EMA sampling. In addition, as previously mentioned, SMMT communities experience unique sociostructural challenges, such as unemployment, homelessness, forced displacement, and community violence [59]. These systems of power may operate dynamically and render difficulties in participating fully and equitably in hazardous alcohol use prevention programs [60]. Finally, the real-time tracking of alcohol use behaviors of participants may give rise to reporting bias. In the context of alcohol-related stigma, social desirability biases may subject participants to aligning their responses to the expectations of societal norms around alcohol consumption; however, the use of breathalyzers will help to protect against self-report bias.

Prior studies have also reported concerns for temporal bias, where participants were reluctant to complete location- and time-based–triggered EMA surveys due to the inconvenient times at which the surveys were sent. Similarly, EMA studies related to substance use have mentioned challenges with the time frame for EMA sampling [61]. In this study, EMA assessments will occur between 11 AM and 11 PM to avoid disturbing participants. However, participants in prior studies have discussed that these hours may not be representative of the time frames when drinking occurs because alcohol use may occur later at night, along with variations in mood and social activities. Thus, we may explore the potential options for personalized hours of EMA sampling for participants. Breathalyzer device loss may also pose a challenge. However, unlike prior EMA studies that distributed mobile phones and experienced challenges with device loss [62], our study enables participants to use their existing smartphones to use the app, which will reduce instances of device loss or misplacement.

We plan to follow this study with dissemination and implementation research that takes the most effective approach identified here and distributes it to a wider population of SMMT individuals. Overall, by reducing hazardous alcohol use among emerging adult SMMT individuals, we hope to reduce the rates of alcohol-associated HIV transmission among this population considered to be at high risk.

